**Methods and analysis:**

This single-center, assessor-blinded RCT will enroll 50 participants randomized 1:1 to control (health education + lumbopelvic manipulation) or experimental group (same plus Baduanjin). The control group will receive lumbopelvic manipulation (15 min/session, three times per week), while the experimental group will receive the same manipulation plus supervised Baduanjin exercise (12 min/session, three times per week) for 4 weeks. The 4-week intervention is followed by follow-up assessments at weeks 8 and 12. Primary outcome: pain intensity (Numerical Pain Rating Scale, NPRS). Secondary outcomes: functional disability (Oswestry Disability Index, ODI), quality of life (SF-36), and sEMG parameters (%MVIC and mean power frequency, MPF) of the lumbar extensors (erector spinae and multifidus) and abdominal wall muscles (rectus abdominis, external/internal oblique, and transversus abdominis). Assessments at baseline (week 0) and week 4; NPRS, ODI, SF-36 also at weeks 8 and 12.

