#### Withdrawal/dropout criteria

2.4.4

(1) Participants are found not to meet the inclusion criteria after enrollment; (2) Adherence to the intervention protocol falls below 80% (i.e., missing more than 2 of the 12 scheduled manipulation sessions, or more than 5 of the 28 scheduled Baduanjin sessions), without a valid reason documented by the investigator. Missed sessions may be rescheduled at the discretion of the investigator when the absence is due to unavoidable circumstances (e.g., acute illness or family emergency), but such rescheduling does not reset the adherence count; (3) Participants show poor compliance, including changes to or receipt of other relevant treatments during the trial; (4) Participants request to withdraw or voluntarily withdraw from the trial during the study period.

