#### Experimental group intervention

2.7.2

Participants in the experimental group will receive the same intervention as the control group (health education plus lumbopelvic manipulation), combined with Baduanjin exercise. The Baduanjin protocol will follow the standard version released by the General Administration of Sport of China in 2003 (20). All sessions will be conducted in a quiet, well-ventilated room under the supervision of a trained rehabilitation therapist with a valid rehabilitation therapist license and at least 5 years of clinical experience in postpartum rehabilitation. The full set of eight movements will be performed twice, with a 3-min rest between sets; the eight movements and their key points for postpartum women are summarized in Table 2 each supervised session will last 12 min and will be completed once daily on the days when participants attend the treatment sessions (i.e., three times per week). The frequency of three supervised sessions per week was chosen for two main reasons. First, it aligns the Baduanjin practice with the lumbopelvic manipulation sessions, ensuring standardized delivery of the combined intervention. Second, requiring daily on-site attendance would impose a substantial burden on postpartum women who are caring for newborns, potentially compromising adherence.

**Table 2 T2:** The eight movements of the optimized Baduanjin protocol and key points for postpartum women.

Movement	Name	Key point for postpartum women
1	Holding the hands high with palms up	Avoid excessive lumbar extension; engage core muscles
2	Drawing the bow to shoot the vulture	Keep shoulders relaxed; maintain a neutral pelvic position
3	Holding one arm aloft	Control breathing; avoid trunk twisting
4	Looking backwards	Rotate from the thoracic spine, not from the lumbar spine
5	Swinging the head and tail	Coordinate hip movement; avoid deep squatting
6	Holding the feet to strengthen the kidneys	Keep slight knee flexion; avoid rounding the lower back
7	Clenching fists and glaring angrily	Keep the pelvic floor relaxed; avoid breath-holding
8	Bouncing on the toes	Land softly; maintain core tension throughout

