To monitor correct exercise performance, the therapist will provide standardized verbal cues during each session (e.g., “breathe deeply into your lower abdomen and gently draw your navel toward your spine,” “maintain a neutral pelvic position without arching your lower back”). Participants will receive weekly one-on-one assessments of movement quality; signs of inadequate core engagement—such as visible abdominal bulging, excessive lumbar lordosis, or breath-holding during movements—will be documented and addressed through individual instruction. Participants will be instructed not to perform additional Baduanjin practice outside the supervised sessions, and adherence to this restriction will be monitored through daily exercise logs. This restriction was implemented to ensure that the intervention effect can be attributed to the prescribed combined protocol rather than to unsupervised variable-dose practice. By standardizing the frequency, intensity, and supervision of Baduanjin sessions across participants, we minimize confounding from differential home practice, thereby enhancing the internal validity of the trial. During the follow-up period (weeks 4–12), participants will be instructed not to resume Baduanjin practice outside the study protocol. Adherence to this restriction will be monitored through the same daily exercise logs maintained during the intervention phase, which will be reviewed at each follow-up visit (weeks 8 and 12).

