### Data management and quality control

2.10

All clinical data collected by qualified physicians will be entered into a dedicated electronic database, with participant identities replaced by numerical codes. The principal investigator will be responsible for data quality at the study site. Quarterly investigator meetings will address trial-related issues and ensure procedural consistency. Telephone reminders for scheduled visits and assessments will be provided to participants to improve adherence. To monitor adherence to the protocol restriction on unrelated physiotherapy and medications, the following measures will be implemented: (1) participants will be instructed to maintain a daily log recording any additional treatments or medications used during the intervention period; (2) at each study visit (weeks 4, 8, and 12), participants will be systematically asked about their use of other therapies; and (3) weekly telephone calls will be made to reinforce the protocol requirements. Any deviation from the protocol will be recorded in the case report form and reported to the principal investigator. Participants who fail to comply with the protocol will be considered for withdrawal according to the predefined criteria.

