### Statistical analysis

2.12

All statistical analyses will be performed using SPSS version 26.0. Primary analyses will be conducted on an intention-to-treat (ITT) basis, including all randomized participants in their originally assigned groups regardless of protocol adherence or withdrawal. Missing data will be handled via multiple imputation (MI), the gold-standard approach for missing continuous clinical outcome data in randomized controlled trials. Last observation carried forward (LOCF) will not be adopted in the present study, as this single-imputation method is prone to bias and has been widely discouraged in contemporary statistical guidelines. Continuous variables will first be tested for normality using the Shapiro-Wilk test. Normally distributed data will be reported as mean ± standard deviation (SD), whereas non-normally distributed data will be presented as median (first quartile, third quartile) [M (P25, P75)]. For within-group comparisons, paired-sample t-tests will be applied to normally distributed data, and Wilcoxon signed-rank tests to non-normally distributed data. For between-group comparisons at baseline, independent-sample t-tests will be used for normally distributed data, and Mann-Whitney U tests for non-normally distributed data. To compare post-intervention outcomes between the two groups, analysis of covariance (ANCOVA) will be performed, with baseline values as covariates to adjust for potential baseline imbalance. In addition, potential confounding variables—including postpartum duration (months since delivery), age, and baseline outcome values—will be recorded and considered as covariates in the primary analyses where appropriate. Exploratory correlation analyses will employ Pearson or Spearman correlation coefficients, as appropriate, to examine associations among post-intervention pain intensity (NPRS), the Oswestry Disability Index (ODI), the SF-36, core muscle activation (%MVIC), and mean power frequency (MPF). These analyses are hypothesis-generating and will be interpreted with caution; formal corrections for multiple comparisons will not be implemented. All tests will be two-sided, and a *P*-value < 0.05 will indicate statistical significance. Given the exploratory nature of these analyses and the multiple comparisons involved, the results should be interpreted as hypothesis-generating, and any statistically significant findings will require confirmation in future studies.

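### The Baduanjin adherence rule counts 28 scheduled sessions with 5 allowed misses, but the protocol schedules 12, for which the 80% limit is 2 missed

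*Protocol article*

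**What the plan says.** Section 2.4.4 (Withdrawal/dropout criteria) lists adherence below 80% as a ground for withdrawal and spells it out as "missing more than 2 of the 12 scheduled manipulation sessions, or more than 5 of the 28 scheduled Baduanjin sessions". It exempts shortfalls with a documented valid reason, since the criterion applies only "without a valid reason documented by the investigator".

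The schedule is given elsewhere:

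- The abstract describes "supervised Baduanjin exercise (12 min/session, three times per week) for 4 weeks".
- Section 2.7.2 says each session "will be completed once daily on the days when participants attend the treatment sessions (i.e., three times per week". It explains why a daily schedule was not chosen: "requiring daily on-site attendance would impose a substantial burden on postpartum women who are caring for newborns".
- Section 2.7.2 also rules out home practice: "Participants will be instructed not to perform additional Baduanjin practice outside the supervised sessions". It repeats the restriction for weeks 4–12.
- Section 2.7.1 sets manipulation at three sessions a week over four weeks.

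On the use of the rule, section 2.10 says: "Participants who fail to comply with the protocol will be considered for withdrawal according to the predefined criteria". Section 2.12 describes the primary analysis as intention to treat, "including all randomized participants in their originally assigned groups regardless of protocol adherence or withdrawal".

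**The concern.** The Baduanjin clause counts against a number of sessions that the protocol does not schedule. The manipulation clause in the same sentence is correct and applies to both arms, so the error lies only in the part that governs the experimental arm.

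Baduanjin is the sole difference between the arms, so its adherence count is the trial's measure of whether the tested component was delivered. Two things depend on the threshold: decisions to withdraw experimental-arm participants, which section 2.10 refers back to these criteria, and the Baduanjin adherence that will be reported, if 28 is carried into the denominator. A third effect is conditional. If withdrawn participants are not followed up, their outcome data are lost and must be imputed. The article does not say whether they are followed.

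**Working it through.** **Inputs**

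- Adherence threshold: 80% (section 2.4.4).
- Stated counts: manipulation 12 scheduled, at most 2 missed; Baduanjin 28 scheduled, at most 5 missed (section 2.4.4).
- Frequency and duration: 3 per week for 4 weeks, for manipulation (section 2.7.1) and for Baduanjin (abstract; section 2.7.2). The intervention phase is 4 weeks (section 2.1).
- No Baduanjin outside supervised sessions, during treatment or follow-up (section 2.7.2).

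**Formulas**

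Scheduled sessions n = sessions per week × weeks. The limit is the largest number missed, k, for which (n − k)/n ≥ 0.80.

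**Step 1: the plan's own figures.** The manipulation clause reproduces: n = 3 × 4 = 12, k = 2. The Baduanjin limit of 5 is right for a base of 28, but the base does not follow from the schedule.

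| Basis | n | Limit k | Adherence at k missed | Adherence at k + 1 missed |
|---|---|---|---|---|
| Manipulation, 3 × 4 | 12 | 2 | 10/12 = 83.3% | 9/12 = 75.0% |
| Baduanjin as stated | 28 | 5 | 23/28 = 82.1% | 22/28 = 78.6% |
| Baduanjin as scheduled, 3 × 4 | 12 | 2 | 10/12 = 83.3% | 9/12 = 75.0% |

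**Step 2: can any reading give 28?** Daily practice does (7 × 4 = 28), but section 2.7.2 rejects daily attendance and bars home sessions. Counting the two sets in each session separately gives 2 × 12 = 24, with a limit of 4 (20/24 = 83.3%; 19/24 = 79.2%). Nothing in the article yields 28. The 28 and 5 form a consistent pair for a daily schedule, so a garbled character in the text is an unlikely explanation.

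**Step 3: what the clause does in practice**

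*Reading 1, attendance measured against 28.* Full attendance is 12/28 = 42.9%, so every participant fails an 80% rule. This counts 28 − 12 = 16 sessions that are never arranged.

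*Reading 2, the limit of 5 applied to the 12 real sessions.*

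| Baduanjin sessions missed | Attended | Below 80%? | Flagged by more than 5 missed? |
|---|---|---|---|
| 2 | 10/12 = 83.3% | no | no |
| 3 | 9/12 = 75.0% | yes | no |
| 4 | 8/12 = 66.7% | yes | no |
| 5 | 7/12 = 58.3% | yes | no |
| 6 | 6/12 = 50.0% | yes | yes |

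A participant who misses 3 or more whole visits is still caught by the manipulation clause. The gap in reading 2 is therefore confined to those who come for manipulation and skip the exercise on 3, 4 or 5 days.

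**The case against.** The contradiction itself is hard to dispute. The case on the other side is about its weight.

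- *The 80% figure is the governing rule and the counts only explain it, so a site could apply 80% to the 12 real sessions.* This is possible, but only by setting aside the counts the section prints. The text then gives two different answers for a participant who misses 3, 4 or 5 sessions.
- *No site would withdraw a fully attending participant at 12/28.* This stands. Reading 1 shows that the clause cannot be taken literally; it is not a likely event.
- *The gap in reading 2 is narrow.* This also stands. It needs Baduanjin to be skipped on days when manipulation is attended, and the article gives no figure for how often that would happen. The separate poor-compliance criterion offers another route, though a less specific one.
- *The inference is protected.* This largely stands. Intention to treat keeps all randomized participants, missing data are multiply imputed, withdrawal is discretionary, and the article describes no analysis set defined by adherence. Neither the sample size nor the primary comparison uses the 28 or the 5.
- *Some of the harm rests on material not shown.* This is fair. Whether the case report form or log uses 28, and whether withdrawn participants are followed, is unknown.

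These points limit the consequences. None of them makes 28 and 5 correct.

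**Conclusion.** The Baduanjin clause in section 2.4.4 is wrong as written. The scheduled number is 12, not 28, and the 80% limit is 2 missed, not 5. Under the stated limit, Baduanjin attendance as low as 58.3% would go unflagged in a participant who keeps up manipulation, against an intended floor of 80%.

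The conclusion rests only on the schedule in the abstract and section 2.7.2 and on the 80% threshold. That the figures come from a daily schedule is a plausible inference, but the finding does not need it. The effect falls on withdrawal decisions in the experimental arm and, if 28 is used as the denominator, on reported adherence. Membership of the primary analysis set is unaffected. The error should be corrected, but it does not threaten the design.

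**What to change.** In section 2.4.4, change the Baduanjin limit to more than 2 of 12 sessions, the same as for manipulation. Then 10/12 = 83.3% passes and 9/12 = 75.0% does not. Check that the case report form, the adherence log and the planned adherence summary all use 12 as the Baduanjin denominator, and correct any that do not.

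The cost is a one-line protocol correction plus matching form wording where needed. The design, sample size and analysis stay as they are.

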### Randomization

2.5

Eligible participants will be randomly assigned in a 1:1 ratio to either the control or experimental group using a computer-generated block randomization sequence with a block size of 4 or 6 (randomly varying). The randomization sequence will be generated by a designated biostatistician independent of the study team using SPSS.

To ensure allocation concealment, a research coordinator not involved in participant recruitment will prepare sequentially numbered, opaque, sealed envelopes. Each envelope will contain the group assignment corresponding to the participant's sequential number. Envelopes will be opened in sequential order only after the participant has provided written informed consent, completed all baseline assessments (including demographic characteristics, pain intensity measured by the Numerical Rating Scale [NPRS], functional status assessed by the Oswestry Disability Index [ODI], and quality of life evaluated by the 36-Item Short Form Health Survey [SF-36]), and met all eligibility criteria. The group assignment will be recorded immediately thereafter.

### Blinding

2.6

Given the nature of manual therapy and Baduanjin exercise, blinding of participants and treating therapists will not be feasible. However, outcome assessors, data collectors, and the statistician will remain blinded to group allocation throughout the trial. Unblinding will be permitted only in the event of a serious adverse reaction. Should unblinding occur, the following procedures will be followed: (1) the investigator who initiated the unblinding will immediately document the date, time, reason, and the identity of the person who was unblinded; (2) the unblinding event will be recorded in the participant's case report form and in a separate Unblinding Log maintained by the principal investigator; and (3) the principal investigator will notify the institutional ethics committee of the unblinding event within 24 h. The participant may continue in the trial at the discretion of the investigator and the ethics committee.

### Interventions

2.7

#### Control group intervention

2.7.1

Participants in the control group will receive (1) health education on low back pain management, which will cover posture guidance, weight control, and proper techniques for daily activities such as breastfeeding, lifting, sitting, and standing, and (2) lumbopelvic manipulation therapy.

The manipulation therapy will be performed by a licensed therapist with at least 5 years of experience in musculoskeletal and postpartum rehabilitation. Before each session, the therapist will palpate key bony landmarks—including the anterior superior iliac spines (ASIS), iliac crests, posterior superior iliac spines (PSIS), ischial tuberosities, pubic symphysis, and lumbar spinous and transverse processes—to identify pelvic asymmetry and lumbar spine malalignment.

The treating therapist will perform the manipulation, while a separate assessor (also a licensed therapist, blinded to the treatment session number) will perform the reassessment of bony landmarks after each step to determine whether symmetry has been achieved.

The theoretical rationale for these manipulative techniques—including the biomechanical and neurophysiological basis of pelvic micro-adjustment and segmental lumbar mobilization, their mechanisms of action, and their adaptation for postpartum women—is provided in Supplementary file 1, along with full reference citations. The detailed step-by-step manipulation protocol, including specific patient positioning, therapist hand placement, force application, and adjustment criteria for each component, is also provided in Supplementary file 1 to enhance reproducibility while keeping the main text concise. Figure 2 presents the flowchart of this manual therapy procedure.

**Figure 2 F2:**
[figure not shown]
Flowchart of the manual therapy.

The treatment will be administered three times per week in 15-min sessions over four consecutive weeks. To ensure consistency, all treating therapists will undergo a standardized training program, and technique performance will be monitored through regular case reviews and video-based assessments.

#### Experimental group intervention

2.7.2

Participants in the experimental group will receive the same intervention as the control group (health education plus lumbopelvic manipulation), combined with Baduanjin exercise. The Baduanjin protocol will follow the standard version released by the General Administration of Sport of China in 2003 (20). All sessions will be conducted in a quiet, well-ventilated room under the supervision of a trained rehabilitation therapist with a valid rehabilitation therapist license and at least 5 years of clinical experience in postpartum rehabilitation. The full set of eight movements will be performed twice, with a 3-min rest between sets; the eight movements and their key points for postpartum women are summarized in Table 2 each supervised session will last 12 min and will be completed once daily on the days when participants attend the treatment sessions (i.e., three times per week). The frequency of three supervised sessions per week was chosen for two main reasons. First, it aligns the Baduanjin practice with the lumbopelvic manipulation sessions, ensuring standardized delivery of the combined intervention. Second, requiring daily on-site attendance would impose a substantial burden on postpartum women who are caring for newborns, potentially compromising adherence.

**Table 2 T2:** The eight movements of the optimized Baduanjin protocol and key points for postpartum women.

Movement	Name	Key point for postpartum women
1	Holding the hands high with palms up	Avoid excessive lumbar extension; engage core muscles
2	Drawing the bow to shoot the vulture	Keep shoulders relaxed; maintain a neutral pelvic position
3	Holding one arm aloft	Control breathing; avoid trunk twisting
4	Looking backwards	Rotate from the thoracic spine, not from the lumbar spine
5	Swinging the head and tail	Coordinate hip movement; avoid deep squatting
6	Holding the feet to strengthen the kidneys	Keep slight knee flexion; avoid rounding the lower back
7	Clenching fists and glaring angrily	Keep the pelvic floor relaxed; avoid breath-holding
8	Bouncing on the toes	Land softly; maintain core tension throughout

To monitor correct exercise performance, the therapist will provide standardized verbal cues during each session (e.g., “breathe deeply into your lower abdomen and gently draw your navel toward your spine,” “maintain a neutral pelvic position without arching your lower back”). Participants will receive weekly one-on-one assessments of movement quality; signs of inadequate core engagement—such as visible abdominal bulging, excessive lumbar lordosis, or breath-holding during movements—will be documented and addressed through individual instruction. Participants will be instructed not to perform additional Baduanjin practice outside the supervised sessions, and adherence to this restriction will be monitored through daily exercise logs. This restriction was implemented to ensure that the intervention effect can be attributed to the prescribed combined protocol rather than to unsupervised variable-dose practice. By standardizing the frequency, intensity, and supervision of Baduanjin sessions across participants, we minimize confounding from differential home practice, thereby enhancing the internal validity of the trial. During the follow-up period (weeks 4–12), participants will be instructed not to resume Baduanjin practice outside the study protocol. Adherence to this restriction will be monitored through the same daily exercise logs maintained during the intervention phase, which will be reviewed at each follow-up visit (weeks 8 and 12).

